### Eligibility criteria {10}

All subjects will undergo initial screening by ophthalmologists and investigators before enrollment. This screening will include inquiries about general health condition, family and disease history, allergies, and current medications. Potential subjects who meet these preliminary criteria will then be further assessed for ocular health and lifestyle habits based on the established inclusion and exclusion criteria.

Inclusion criteria are as follows:Age: 6–10 years old;Spherical equivalent (SE) in either eye: >  − 0.50D and ≤  + 0.75D (based on the average value of automatic refraction under cycloplegia);Astigmatism in either eye: ≤ 1.50D;At least 1 h of near work every day, including non-learning (TV, games, etc.); learning (online learning, punching in); and reading;The uncorrected visual acuity in either eye: ≥ 4.9, and the best corrected visual acuity: ≥ 5.0;Never participated in any clinical trial of myopia control within 3 months or used myopia prevention methods, such as multi-point design defocus glasses, low concentration atropine, repeated low-level red light (RLRL), etc.No manifest strabismus was observed.

Exclusion criteria as follows:Failure to comply with the protocol to obtain reliable study measurements.There is an eye disease that can affect refractive development, such as retinal disease, cataract, and ptosis;The existence of systemic or neurodevelopmental conditions that may affect refractive development;Eye or systemic drugs known to affect the development of myopia or visual acuity through effects on retinal regulation amplitude or intraocular pressure are being used.

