#### Exploratory outcomes

*Time from randomization to occurrence of myopia (time-to-event outcome)*: The time from randomization to the occurrence of myopia will be measured as a time-to-event outcome. This endpoint will provide further insights into how quickly DIST delays the onset of myopia compared to the control group.*The association between near-work duration at home and myopia onset*: The duration of near-work activities (e.g., reading, using electronic devices) at home will be correlated with the onset of myopia to investigate environmental factors influencing myopia development. This data will help clarify the role of lifestyle factors in conjunction with DIST intervention.*The association between device usage duration and myopia onset*: The duration of DIST device usage will be correlated with the onset of myopia to explore potential dose–response relationships. This will determine whether longer usage of DIST is associated with a greater effect on myopia prevention, while controlling for other near work behaviors.*Changes in choroidal thickness (ChT) (µm) at 6 and 12 months follow-ups*: Changes in choroidal thickness will be monitored as an exploratory endpoint to assess the potential underlying physiological mechanisms of DIST technology in myopia prevention. Changes in choroidal thickness or blood flow as biomarkers of myopia progression are of significant importance in myopia prevention and control research.*Side effects and adverse events*: The occurrence of side effects and adverse events will be closely monitored throughout the study to ensure the safety of the DIST intervention. This will include any ocular or systemic issues reported by participants, and the severity of these events will be recorded.

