## Assignment of interventions: allocation

### Sequence generation {16a}

A computer-generated randomization schedule will be used to allocate the 192 participants into one control group and two experimental groups in a 1:1:1 ratio. The randomization will be performed using simple randomization without stratification. The sequence will be generated by an independent statistician to ensure allocation concealment and minimize potential bias in the assignment process.

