## Data collection and management

### Plans for assessment and collection of outcomes {18a}

At baseline and during each follow-up, researchers will provide paper-based questionnaires for guardians to complete, and the results will be entered into a spreadsheet for analysis. All other clinical assessments will be performed by experienced clinicians using relevant measuring instruments (as specified in item 12). Measurements will be repeated to ensure the reliability and validity of the data collection. Meanwhile, patients’ general information, medical history, baseline and follow-up results, adverse event reports, and trial summaries will be recorded in the CRFs by researchers on time. All researchers and clinicians will undergo training on participant recruitment, assessment, intervention, and data backup before participating in the study.

Cycloplegic autorefraction will be performed using the Topcon KR800 autorefractor unit following the cycloplegia regimen of 1% cyclopentolate (Cyclogyl, AlconConvreur). The procedure involves administering two drops of 1% cyclopentolate separated by a 5-min interval, followed by a 30-min resting period after the final instillation. Complete cycloplegia is confirmed by the absence of fluctuation in retinoscopy findings under cycloplegic conditions in children or by performing autorefraction combined with careful subjective refraction. Spherical equivalent is calculated as spherical power plus half of the cylinder power. Cycloplegic measurements will be performed at baseline, the 6-month follow-up, and the 12-month follow-up to assess the primary outcome.

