## Statistical methods

### Statistical methods for primary and secondary outcomes {20a}

Analysis of primary outcomeIn this participant-based study, the primary outcome is the proportion of myopia onset. This outcome is measured as a binary (nominal) variable. Participants are classified as either having experienced the onset of myopia (Yes) or not (No), based on whether their cycloplegic spherical equivalent refractive error reaches or exceeds − 0.50 D in either eye at the 1-year follow-up. This is a single endpoint measure, assessed once at the end of the 1-year follow-up period. It provides a proportion of participants who experience the onset of myopia. To test the effectiveness of DIST on the primary outcomes, logistic regression including trend analysis will be used, which can both examine the overall relationship and detect potential trends related to different treatments. In addition, covariates such as baseline spherical equivalent refractive error, age, gender, and study group (Intervention vs. Control) will be included to ensure a parsimonious logistic regression model while controlling for factors known to influence myopia onset and progression.The primary analysis will be conducted on the ITT population, which is defined as all randomized participants with at least one post-baseline measurement. For all analyses, the underlying model assumptions will be rigorously evaluated. For instance, when applying logistic regression to assess the binary primary outcome, we will verify the linearity of the logit for continuous covariates using methods such as the Box–Tidwell test, assess multicollinearity via variance inflation factors (VIF), and examine residuals and influence statistics (e.g., Cook’s distance) to identify any influential outliers. Missing data will be addressed using multiple imputations by chained equations under the assumption of data missing at random (MAR), with sensitivity analyses planned to assess the impact of outliers, nonadherence, and loss to follow-up.Analysis of secondary outcomesThe secondary outcomes are intended to capture aspects of the intervention effect that are not fully reflected by the primary outcome. For example, even if the primary outcome (myopia onset) does not show a statistically significant difference, significant changes in spherical equivalent or axial length may still be observed, thereby indicating a potential benefit of the intervention in slowing myopia progression.For the three secondary outcomes: (1) the proportion of fast progressors over 1 year, (2) changes in spherical equivalent progression, and (3) changes in AL (mm) at each follow-up point, the following statistical procedures will be employed:Proportion of fast progressors (binary outcome)This endpoint will be analyzed using logistic regression. The model will estimate the odds of being classified as a fast progressor over 1 year, comparing the intervention group to the control group. Covariates to be included in the model are baseline spherical equivalent refractive error (continuous), age (continuous), and gender (categorical), as these factors have been shown in prior research to influence myopia progression. The study group (intervention vs. control) will be the primary factor of interest. These covariates are selected based on their theoretical relevance and empirical support, ensuring a parsimonious model that controls for potential confounding without overfitting.Changes in spherical equivalent progression (continuous outcome)The change in spherical equivalent progression over time will be analyzed using a repeated measures mixed-effects model. This model will account for within-subject correlations across multiple follow-up points and will include fixed effects for the treatment group, time (as a categorical or continuous variable depending on the observed pattern), and the interaction between treatment and time. Baseline spherical equivalent refractive error, age, and gender will be included as covariates to adjust for initial differences and known predictors of refractive change. The rationale for these covariates is their established association with myopia progression, ensuring that the model is both explanatory and parsimonious. Model selection procedures, such as stepwise backward elimination based on the Akaike Information Criterion (AIC) or likelihood ratio tests, will be applied to refine the final model.Changes in AL (mm)Similar to the spherical equivalent endpoint, changes in axial length (measured in mm) at each follow-up will be analyzed using a repeated measures mixed-effects model or an analysis of covariance (ANCOVA) for longitudinal data. The model will include fixed effects for treatment, time, and their interaction. Covariates will include baseline axial length, baseline spherical equivalent, age, and gender. These factors are chosen because they are known to influence ocular growth and, consequently, axial elongation. As with the other endpoints, a parsimonious model will be achieved by using stepwise selection methods or likelihood ratio tests to retain only covariates that contribute significantly to explaining the variation in axial length change.The results of these analyses will be presented as adjusted odds ratios with 95% confidence intervals for the binary outcome and as least-squares means (LSMEANS) with standard errors for the continuous outcomes. In addition, p-values will be reported to assess the statistical significance of the observed differences between intervention groups.Analysis of exploratory outcomesTime-to-myopia onset analysisFor comparing the time to myopia onset (time-to-event outcome) among 3 treatment groups, we all create a number-at-risk table and use the Kaplan–Meier method to estimate survival curves, followed by the log-rank test to assess differences statistically.Myopia onset associationsA logistic regression model will be built with myopia onset as the dependent variable and near-work duration, device usage duration, and confounding factors as independent variables. The near-work duration was derived from the near-work log cards and questionnaires, with the daily averages taken for analysis. Odds ratio (OR) and its 95% confidence interval will be estimated to determine associations while controlling for confounding.Dose–response relationship analysisWe will group near work and device usage durations (e.g., by quartiles). Use the Cochrance–Armitage trend test to analyze if there’s a dose–response relationship. Curve fitting (such as polynomial regression) can also be used to further explore the non-linear relationship between them.Choroidal thickness changesFor exploring changes in choroidal thickness during different follow-up periods among three groups, repeated measures analysis of variance (ANOVA) will be used. If significant effects are found, post hoc tests (like Bonferroni or Tukey’s) will determine specific differences.

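### The exploratory time-to-onset comparison rests on an unadjusted log-rank test, although baseline SE is collected and already adjusts the primary onset model; this costs precision and consistency, not validity.

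*Protocol article*

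**What the plan says.** All places are in the Protocol article.

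- **Exploratory outcomes** lists "Time from randomization to occurrence of myopia (time-to-event outcome") and gives its purpose: "This endpoint will provide further insights into how quickly DIST delays the onset of myopia compared to the control group".
- **Statistical methods for primary and secondary outcomes {20a}**, time-to-myopia onset analysis: besides a number-at-risk table, the plan will "use the Kaplan–Meier method to estimate survival curves, followed by the log-rank test to assess differences statistically", across the three groups. Nothing else is named for this outcome.
- **The same section, primary outcome**: in the logistic model for onset, "covariates such as baseline spherical equivalent refractive error, age, gender, and study group (Intervention vs. Control) will be included". The stated reason includes "controlling for factors known to influence myopia onset and progression". Baseline SE, age and gender are also the starting covariates for the fast-progressor, SE-change and axial-length models.
- **Plans for assessment and collection of outcomes {18a}**: "Cycloplegic measurements will be performed at baseline, the 6-month follow-up, and the 12-month follow-up to assess the primary outcome". Table 1 shows no cycloplegic refraction at 3 months.
- **Eligibility criteria {10}**: entry SE lies above −0.50 D and up to +0.75 D, "based on the average value of automatic refraction under cycloplegia". Under **Primary outcome**, onset is SE of at least −0.50 D (myopic) in either eye.
- **Sequence generation {16a}**: "The randomization will be performed using simple randomization without stratification".

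**The concern.** Baseline SE and the event are on the same scale. A child who enters at +0.75 D needs a shift of 0.75 − (−0.50) = 1.25 D to become an event. That is 2.5 times the 0.50 D per year that the plan calls fast progression. A child who enters just above −0.50 D needs almost no shift. Starting SE is therefore likely to be a strong predictor of when onset is seen, and the plan itself treats it as a predictor of whether onset occurs.

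For this outcome neither the design nor the analysis uses that information. Two things are at stake:

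- **Precision.** The comparison leaves unused a covariate that is already in the database.
- **Consistency.** An unadjusted timing result will stand beside an adjusted 12-month result. The two may differ partly because of chance differences in starting SE.

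The log-rank test also gives no estimate of how large the delay is.

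**Working it through.** **1. The plan's own figure.** Inputs from Sample size {14}: 0.54 vs 0.21, margin 0.05, α = 0.0125 (reproduces as one-sided), power 80%, dropout 20%.

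n = [0.54×0.46 + 0.21×0.79] × (2.241 + 0.842)² / (0.54 − 0.21 − 0.05)² = 0.4143 × 9.505 / 0.0784 ≈ 50.2, so 51. Then 51/0.80 = 63.75, so 64 per arm and 192 in total. The stated figures reproduce. They concern the binary primary outcome; no power is stated for time to onset. Under proportional hazards the planning rates imply HR = ln(0.79)/ln(0.46) = 0.30.

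**2. Size of chance imbalance.** With 64 vs 64, the standard error of the standardised baseline difference is √(2/64) = 0.177. P(|difference| > 0.25 SD) = P(|Z| > 1.41) ≈ 16% per comparison. If the hazard ratio per SD of baseline SE is h (assumed 1.5, 2.0 or 3.0), a one-standard-error imbalance multiplies the unadjusted HR by h^0.177 = 1.07, 1.13 or 1.21. Applied to 0.30, this gives about 0.32 to 0.36.

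**3. Validity of the log-rank test.** Simulated under no effect (50 per arm, onset seen at 6 and 12 months, nominal two-sided 0.025), it rejects in 0.027 to 0.029 of trials, within simulation error of nominal.

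**4. Power from adjusting, one device arm vs control.** Set-up: 51 per arm; baseline SE normal around +0.25 D with SD 0.35 D, truncated to the entry range; normal 1-year SE change with arm means set to give the event rates; half the drift and variance by 6 months; two-sided 0.025. The log-rank test is compared with a likelihood-ratio test for arm in a complementary log-log model by visit that contains baseline SE. The baseline spread and SD of change are assumptions, as the document gives neither.

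| SD of change | 54% vs 21%, nominal | 54% vs 30% (assumed), nominal | Null rejection, adjusted test | Size-corrected gain at 21% / 30% |
|---|---|---|---|---|
| 0.35 D | 0.88 → 0.96 | 0.53 → 0.75 | 0.046 | 7 / 10 points |
| 0.50 D | 0.88 → 0.94 | 0.55 → 0.67 | 0.036 | 6 / 8 points |
| 0.80 D | 0.85 → 0.90 | 0.53 → 0.59 | 0.034 | 1 / 2 points |

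The adjusted test rejects too often under the null (nominal 0.025), so part of the nominal gain is test size. The last column removes that part. A repeat of the size-corrected runs gave 9, 5 and 4 points at 21% and 15, 8 and 6 at 30%. The direction is stable, but individual entries are uncertain by several points.

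**5. Three-group test.** After size correction, the gain for SDs of 0.35, 0.50 and 0.80 D is about 12, 7 and −1 points with both device arms at 30%, and 3, 2 and −1 with both at 21%.

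**6. Cross-check by prognostic strength** (proportional hazards, 50 per arm, not size-corrected). With h = 1.0 there is no gain (0.892 → 0.885 at 54% vs 21%). With h = 2.0 power goes from 0.908 to 0.943 at 54% vs 21% and from 0.587 to 0.695 at 54% vs 30%. A log-rank test stratified by thirds of baseline SE reaches 0.661 in the last case, so it recovers part of the gain.

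**The case against.** The case for leaving the plan alone is substantial.

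- **The test is valid and the endpoint exploratory.** No alpha, power target or confirmatory claim attaches to it. This stands and limits the weight of the point.
- **A reader might infer that chance imbalance biases the result.** The document does not support that. Under randomisation such imbalance is random error, already allowed for in the null distribution; step 3 shows the error rate holds.
- **A reader might infer that the trial's main aim is left unadjusted.** It is not. The Primary outcome section gives the delay question to the 12-month proportion, and that model includes baseline SE. With cycloplegic refraction only at 6 and 12 months, the timing analysis mainly adds at which of the two visits onset was first seen.
- **A reader might infer an internal contradiction.** There is none. The plan makes no rule that every analysis be adjusted, and other exploratory analyses, such as the trend test and the choroidal-thickness ANOVA, are simple too.
- **The gain is assumption-driven.** This also stands. The simulations use one SE value per child, whereas onset is defined in either eye. The plan's test is across three groups, and 54% vs 30% is not in the plan.
- **The SAP may add a model.** It may, but the point does not rest on missing detail. The article fixes a particular test that leaves out a covariate it relies on elsewhere.

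**Conclusion.** The point holds as a low-priority improvement to an exploratory analysis. The unadjusted log-rank test is valid, but it leaves unused a covariate that the plan treats as a driver of onset, and it sits awkwardly beside an adjusted primary analysis.

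The size-corrected pairwise gain from adjusting is about 7, 6 and 1 points at 54% vs 21%, and about 10, 8 and 2 points at an assumed 54% vs 30%. These figures rest on the assumed baseline spread and SDs of change. The gain is zero if baseline SE does not predict onset, and may vanish for the three-group test at the largest SD.

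The nominal gain of 22 points (0.53 to 0.75) should not be taken at face value, because part of it comes from the adjusted test exceeding its nominal size. Nor do the results justify dropping the log-rank test.

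**What to change.** In section {20a}, time-to-myopia onset analysis, keep the Kaplan–Meier curves, the number-at-risk table and the log-rank test. Add a grouped-time hazard model (complementary log-log by visit) with study group, baseline SE, age and gender. A model by visit suits data in which onset is confirmed only at 6 and 12 months better than a continuous-time Cox model does. Report the adjusted hazard ratio with its 95% CI, and check the size of the test at this sample size, for example by permutation. A log-rank test stratified by baseline SE is a simpler alternative.

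The cost is a sentence or two of text and a few lines of code, with no new data. The downsides are that the hazard ratio is conditional on the covariates and so will not match the unadjusted curves exactly, proportionality must be checked, and the model-based test is slightly liberal unless calibrated.

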## Interventions

### Explanation for the choice of comparators {6b}

The choice of comparators in this study was guided by the need to evaluate the efficacy of long-term use of DIST and its potential enhancement when combined with the optical defocusing technique in delaying the onset of myopia. This group (daily near work without DIST) serves as the baseline comparator, reflecting typical daily activities that involve prolonged near work without specific interventions. Prolonged near work is a well-documented risk factor for myopia development, but its role in the absence of compensatory measures, such as DIST, remains an important baseline for understanding the natural progression of myopia onset. This control group enables the evaluation of whether DIST alone provides a protective effect against myopia development. By maintaining their habitual near work activities, participants in this group help establish a reference for comparing the effectiveness of interventions.

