### Intervention description {11a}

There are two intervention groups in our study: the DIST Group (use of DIST alone) and the Combined Intervention Group (DIST and Optical Defocusing Technique). Participants in these two groups will be asked to use the device during near work, including online learning, playing online games, reading, and similar tasks, with a minimum daily usage of 1 h.

The DIST group is included to investigate whether projecting near scenes into the distance can effectively delay the onset of myopia. This group is critical for isolating the specific effect of DIST as a standalone intervention, independent of other factors. The use of DIST aligns with emerging evidence suggesting that increasing outdoor-like visual experiences or reducing accommodative stress may mitigate myopia progression.

The Combined Intervention group (DIST and Optical Defocusing Technique) evaluates the synergistic effect of combining DIST with an optical defocusing technique. DIST and the optical defocusing technique can be integrated simultaneously through the optical path system (Fig. 2). The system contains two Liquid Crystal Display (LCD) screens, one of which is used to achieve distant-image display, while the other is used to achieve defocus intervention. LCD-1 functions as the object for the distant-image display, while half-mirror-2, the curved mirror, and the lens together form a convex lens optical system. Based on the principles of geometric optics, LCD-1 is positioned within one focal length of this convex lens system. As a result, the light rays entering the eye are divergent, forming an erect, magnified virtual image that enables the perception of a distant image. Similarly, LCD-2 acts as the object for the defocusing pathway, while half-mirror-1, half-mirror-2, and the curved mirror collectively form a convex lens optical system. By positioning LCD-2 between one and two focal lengths of the convex lens optical system, the light rays entering the eye become convergent, thereby achieving defocusing intervention.

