### Methods for additional analyses (e.g., subgroup analyses) {20b}

Subgroup analysis will be conducted based on the total duration of near work and the usage duration of devices in this study. The aim is to explore the impacts of these two factors on AL growth and the incidence rate of myopia among the subjects.

Firstly, we will divide the subjects into different subgroups according to specific criteria regarding the durations of near work and device usage.

Then, appropriate statistical methods will be employed for the analysis. To analyze the impact on the AL growth, which is a continuous variable, we will consider using analysis of variance (ANOVA) or regression analysis to compare the differences in AL changes among different subgroups and to determine whether there are significant associations between the durations of near work/device usage and the AL growth. In this process, relevant covariates such as age, gender, baseline refractive status, and outdoor activity time will be adjusted to control for potential confounding effects.

For the analysis of the impact on the incidence rate of myopia, which is a binary variable, logistic regression will be utilized. The myopia incidence will be set as the dependent variable, while the durations of near work and device usage will be the main independent variables. Additionally, the same set of covariates as mentioned above will be included in the model to account for confounding factors and to obtain more accurate estimates of the odds ratios and their corresponding confidence intervals, which can reflect the strength and significance of the associations between these factors and the myopia incidence.

Furthermore, interaction terms between the durations of near work and device usage might be considered in the models to explore whether there are combined effects of these two factors on the outcomes of interest. Through this comprehensive subgroup analysis, we expect to gain a more detailed and in-depth understanding of how the durations of near work and device usage influence the AL growth and the myopia incidence among the subjects.

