#### Binary outcomes (myopia incidence and proportion of fast progressors)

For binary outcomes, logistic regression will be utilized. Here, the dependent variable will be the incidence of myopia (or classification as a fast progressor), and the primary predictors will be the categorized durations of device usage and near work. The same set of covariates (age, gender, baseline refractive error, outdoor activity time) will be included to adjust for confounding. Odds ratios with corresponding 95% confidence intervals will be calculated to quantify the associations.

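### The exploratory device-use dose–response is assigned to an unadjusted trend test, although the outcome is defined as controlling for other near work, and no adjusted model is given precedence

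*Protocol article*

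**What the plan says.** **The question.** Under Exploratory outcomes, the protocol relates duration of device use to myopia onset in order to explore a dose–response, and qualifies this with "while controlling for other near work behaviors".

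**The test.** The dose–response paragraph of Statistical methods for primary and secondary outcomes {20a} groups near work and device use, for example by quartiles, and then instructs: "Use the Cochrance–Armitage trend test to analyze if there’s a dose–response relationship". It adds optional curve fitting. It names no covariates or strata.

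**The adjusted models.**
- The preceding paragraph of {20a}, on associations with myopia onset, plans a logistic regression with "near-work duration, device usage duration, and confounding factors as independent variables".
- Methods for additional analyses {20b} plans another logistic model in which "the durations of near work and device usage will be the main independent variables", with age, gender, baseline refraction and outdoor time as covariates.
- The subgroup text on binary outcomes plans a third, where "the primary predictors will be the categorized durations of device usage and near work", with the same covariates.

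**The link between the exposures.** Intervention description {11a} says of the two device arms: "Participants in these two groups will be asked to use the device during near work". Explanation for the choice of comparators {6b} states: "Prolonged near work is a well-documented risk factor for myopia development".

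**The concern.** The condition in the outcome definition and the test named for it do not fit together. Device use is not randomised within the device arms. Children are asked for at least 1 h a day, and how far each child goes beyond or falls short of that is the family's choice. Since use takes place during near work, which the protocol itself treats as a risk factor, a crude trend across usage groups mixes any effect of the device with the effect of near work.

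An analyst who follows the dose–response paragraph literally would report the crude trend as the dose–response finding. If that trend and an adjusted odds ratio point in different directions, nothing in the protocol says which to believe. The protocol also says the usage analyses may inform how the device is best used, so a wrongly signed trend could mislead later work.

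**Working it through.** The protocol gives no power or error rate for this test, so there is no stated figure to reproduce.

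**Step 1. Can the named test adjust?** With usage score g (0 to 3 for quartiles) and outcome y (0 or 1), the Cochran–Armitage statistic is

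Z = Σ(gᵢ − ḡ)(yᵢ − ȳ) / √[ȳ(1 − ȳ) Σ(gᵢ − ḡ)²].

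Only g and y enter. The adjusted alternative is logit P(y = 1) = a + b·g + c·w, with w for near work, and tests b/SE(b).

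**Step 2. Inputs.**
- From the protocol: two device arms of 64, so 2 × 64 = 128 children. With the planned 20% dropout, 128 × 0.8 = 102.4, so about 102. Intervention-arm risk is 21%.
- Assumed, because the protocol gives no values: correlation ρ between use d and near work w of −0.5, 0, 0.3, 0.5 and 0.7; near-work odds ratio (OR) of 1.5 or 2.0 per SD; for a beneficial device, OR 0.6 per SD of use.

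**Step 3. Simulation.** w is standard normal; d = ρw + √(1 − ρ²)·e with e an independent standard normal; logit P = ln(0.21/0.79) + ln(near-work OR)·w + ln(device OR)·d. Use is cut into quartiles. There were 1000 trials per setting, and each direction was counted at |z| > 1.96, which is 2.5% nominal per side. The Monte Carlo standard error is √(0.025 × 0.975/1000) = 0.5 percentage points at 2.5% and √(0.3 × 0.7/1000) = 1.4 points near 30%. The adjusted trend here contains near work only.

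**Step 4. Inert device (device OR 1), 128 children.** Each cell gives the result for near-work OR 1.5, then 2.0.

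| ρ | Error counted | Unadjusted | Adjusted |
|---|---|---|---|
| 0 | false harm | 2.7%, 1.4% | 2.5%, 1.2% |
| 0.3 | false harm | 6.6%, 13.6% | 2.6%, 2.5% |
| 0.5 | false harm | 12.2%, 31.2% | 2.1%, 2.4% |
| 0.7 | false harm | 23.2%, 52.1% | 2.2%, 2.5% |
| −0.5 | false benefit | 13.5%, 31.6% | 2.5%, 2.7% |

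With 102 children the pattern is the same. Unadjusted false harm runs from 7.8% (ρ = 0.3, OR 1.5) to 44.0% (ρ = 0.7, OR 2.0). At ρ = −0.5, false benefit is 11.6% and 25.3%.

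**Step 5. Beneficial device (OR 0.6 per SD of use), 128 children.** Share of trials showing benefit, same order of near-work ORs.

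| ρ | Unadjusted | Adjusted |
|---|---|---|
| 0 | 54.2%, 54.1% | 54.5%, 57.1% |
| 0.3 | 36.1%, 23.3% | 50.6%, 50.6% |
| 0.5 | 23.5%, 11.1% | 45.0%, 43.2% |
| 0.7 | 16.1%, 2.1% | 29.0%, 29.6% |
| −0.5 | 84.0%, 92.6% | 45.6%, 40.5% |

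The high unadjusted figures at −0.5 are not real power. They combine the device effect with confounding that favours the device.

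**Step 6. Which near work is meant?** Let total near work W = other near work O + device time D. If logit P = a + b·D + c·W, then logit P = a + (b + c)·D + c·O. The coefficient of device time is b when total near work is held fixed (device time replaces other near work) and b + c when other near work is held fixed (device time is added). The outcome definition says other near work. The simulation treats w generically and does not separate the two. It shows only what happens when whichever near-work measure matters is left out.

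**The case against.** The strongest reply is that the control for near work is already planned. The logistic model in the paragraph just before the dose–response paragraph holds both durations and confounders, and the subgroup sections add two more such models plus an interaction between the durations. A reader might infer that the protocol has no analysis controlling for near work. The documents do not support that, and this part of the reply stands. The fault is confined to one unadjusted test that carries the dose–response label with no order of precedence.

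A second reply concerns direction. A reader might infer that the crude trend must show false harm or hide a benefit, because near work rises with use. The documents do not establish this either. Device time may displace other near work, or may follow compliance with the 1 h minimum under weekly usage checks. The error could then be absent or reversed. This also stands.

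A third reply is that precedence among exploratory analyses is commonly left to an analysis plan that is not shown here. That holds for fine detail. It does not cover a mismatch stated in the protocol itself, where the outcome requires control and the paragraph answering it names a test that cannot give it. Nor do the subgroup models settle the matter: the subgroup text splits device use into two levels at 30 min a day, with thresholds that may be refined at the end of the study, so it fixes no trend.

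Finally, even the adjusted trend has modest power, 29% to 51% in the positive-correlation settings of Step 5. This limits what the analysis can show, but it is no reason to prefer the biased version.

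**Conclusion.** The point holds as a minor one. The test named for the device-use dose–response cannot meet the condition set by the outcome's own definition, and none of the planned adjusted models is designated in its place.

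Under the assumed inputs, the unadjusted trend for an inert device shows false harm in about 7% to 52% of trials at correlations of 0.3 to 0.7, agrees with the adjusted trend at 0, and shows false benefit in about 14% to 32% at −0.5. The adjusted trend stays near 2.5% throughout. These figures rest on correlations and near-work odds ratios that the protocol does not supply, so they show a possible range and not an expected bias for this trial.

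A reader might also infer that the efficacy conclusion is at risk. It is not: the outcome is exploratory, and the primary and secondary comparisons of randomised groups do not use this test. Adjustment would not turn self-selected use into randomised evidence.

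**What to change.** Replace the instruction in the dose–response paragraph of {20a} with one that states the following:

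- The dose–response result is the trend term for device use, as an ordered category score or continuous hours, in the logistic model already planned, fitted among children in the two device arms.
- The model adjusts for other (non-device) near-work duration, as the outcome definition says, and for baseline spherical equivalent, age and gender.
- The result is reported as an odds ratio with 95% confidence interval and takes precedence over any unadjusted trend.
- The Cochran–Armitage test is descriptive only.

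The text should also say whether the recorded near-work duration includes device time. If it does, device time from the backend records has to be subtracted to obtain other near work. The coefficient should then be described as the effect of added device time at a given level of other near work.

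The cost is a few sentences of analysis wording. Backend usage records, near-work log cards, questionnaires and the baseline covariates are already collected, and neither the sample size nor any visit changes.
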